## Abstract

**Background:**

Delayed cerebral infarction (DCI) is a major cause of death and poor neurological outcome in patients with aneurysmal subarachnoid hemorrhage (aSAH). Direct intrathecal therapies with fibrinolytic and spasmolytic drugs have appeared promising in clinical trials. However, access to the subarachnoid space for intrathecal drug administration is an unsolved problem so far, especially in patients with endovascular aneurysm securing. We investigate a therapy protocol based on stereotactic catheter ventriculocisternostomy (STX-VCS), a new approach to overcome this problem. The primary objective of this study is to assess whether cisternal lavage with urokinase, nimodipine, and Ringer’s solution administered via a stereotactically implanted catheter into the basal cisterns (= investigational treatment (IT)) is safe and improves neurological outcome in patients with aSAH.

**Methods:**

This is a randomized, controlled, parallel-group, open-label phase II trial. Fifty-four patients with severe aSAH (WFNS grade ≥ 3) will be enrolled at one academic tertiary care center in Southern Germany. Patients will be randomized at a ratio of 1:1 to receive either standard of care only or standard of care plus the IT. The primary endpoint is the proportion of subjects with a favorable outcome on the Modified Rankin Scale (defined as mRS 0–3) at 6 months after aSAH. Further clinical and surrogate outcome parameters are defined as secondary endpoints.

**Discussion:**

New approaches for the prevention and therapy of secondary brain injury in patients with aSAH are urgently needed. We propose this RCT to assess the clinical safety and efficacy of a novel therapy protocol for intrathecal administration of urokinase, nimodipine, and Ringer’s solution.

**Trial registration:**

Deutsches Register Klinischer Studien (German Clinical Trials Register), DRKS00015645. Registered on 8 May 2019

## Administrative information

The order of the items has been modified to group similar items (see http://www.equator-network.org/reporting-guidelines/spirit-2013-statement-defining-standard-protocol-items-for-clinical-trials/).

## Introduction

### Background and rationale {6a}

Aneurysmal subarachnoid hemorrhage (aSAH) results from the rupture of an intracranial aneurysm. It represents a medical catastrophe as it confers a high rate of poor neurological outcome and death [1].

Secondary brain injury contributes significantly to poor outcome [2, 3]. In contrast to brain injury incurred during the initial bleeding event, secondary brain injury is potentially amenable to medical treatments. The major mechanism of secondary brain injury is delayed cerebral infarction (DCI) [4, 5]. Days after aSAH, blood break-down products induce prolonged constriction of the cerebral arteries (cerebral vasospasm, CVS) leading to cerebral hypoperfusion and DCI [6, 7]. Owing to the importance of CVS and DCI for the prognosis of aSAH patients, management of CVS is the central treatment focus after aneurysm securing.

Among current treatment options to prevent CVS, the only one to reach level I evidence is oral administration of nimodipine [8, 9]. However, the efficacy is limited [8]. Treatment strategies in established CVS, such as hemodynamic augmentation and endovascular interventions, are commonly applied in clinical practice but are not supported by reliable evidence and come with considerable medical risks (e.g., arterial perforations/dissections, hemorrhagic transformation of brain infarcts, brain edema, cardiovascular events) [10, 11]. Beyond CVS, hydrocephalus is a common sequela of aSAH, typically caused by subarachnoid, intraventricular, and intraparenchymal blood obstructing the cerebrospinal fluid (CSF) pathways, with 6–45% of patients depending on permanent CSF diversion by shunting as a result [12]. Shunt-dependent hydrocephalus is clearly associated with inferior functional outcomes [12, 13]. In summary, despite all efforts, prevention and therapy of secondary brain injury are unsolved medical problems as current treatment options are frequently ineffective.

Intrathecal therapy has been investigated as an alternative treatment approach to interrupt the mechanisms of secondary brain injury for over 30 years [14]. The rationale for intrathecal administration of fibrinolytic drugs, such as urokinase or recombinant tissue plasminogen activator (rtPA), is to remove subarachnoid blood clots and thus the trigger for CVS, while spasmolytic drugs such as nimodipine target the vessels affected by vasospasm directly. Compared to systemically administered drugs, intrathecal delivery brings these agents immediately into contact with their respective target of action. Several clinical trials (mostly non-randomized) have investigated this approach and suggest the general feasibility, safety, and—in part—considerable efficacy of direct intrathecal drug delivery [14].

However, these trials face one major shortcoming: treatments were almost exclusively performed in patients with clipping of the ruptured aneurysm which provides surgical access to the subarachnoid space for implementation of intrathecal therapy. Yet, the majority (approx. 70%) of ruptured aneurysms today is secured by endovascular techniques where no direct access to the brain (e.g., for the placement of a cisternal catheter) is present. Access routes explored so far have proven as either ineffective (e.g., intraventricular drug administration via an external ventricular drain (EVD) [15]) or were associated with significant risks (e.g., drug administration via lumbar catheters [16]). Hence, alternative access routes to the basal cisterns of the brain, the anatomical target region for intrathecal treatments, are required.

To address this “access problem,” we introduced a stereotactic neurosurgical method for catheter implantation into the basal cisterns, stereotactic catheter ventriculocisternostomy (STX-VCS). Based on this method of access, we developed a sequential therapy protocol for cisternal lavage and intrathecal drug delivery. This approach was first applied between September 2015 and October 2016 in individual treatments in 20 patients with aSAH in our institution, with promising results in a retrospective analysis [17]. The access method itself, timing of the intervention, patient selection, sequence of application, and optimal dosing of drugs were refined to prepare the present RCT.

### Objectives {7}

The primary objective of this trial is to assess whether sequential cisternal lavage with urokinase, nimodipine, and Ringer’s solution administered via a stereotactically implanted catheter into the basal cisterns (investigational treatment (IT)) improves neurological outcome in patients with aSAH compared to standard treatment, as measured by the Modified Rankin Scale (mRS).

Key secondary objectives include the assessment of the effect of the IT on rates of DCI and related complications, its effect on further clinical and surrogate endpoints, and its safety. Table 1 presents the secondary objectives and endpoints in detail.

**Table 1 Tab1:** Secondary objectives and endpoints

Secondary objectives	Secondary endpoints
To assess the effect of the IT on neuropsychological outcome	**Neuropsychological outcome** at 6 months following aSAH: - Cognitive performance (Montreal Cognitive Assessment) - Health-related quality of life (SF-36) - Fatigue, anxiety, and depressive symptoms (Frontal Systems Behavior Scale, Multidimensional Assessment of Fatigue, Hospital Anxiety and Depression Scale) - Post-traumatic stress disorder (Impact of Event Scale–R) Return-to-work parameters at 6 months
To assess the effect of the IT on DCI	Rate and severity of **DCI** according to the Vergouwen criteria
To assess the effect of the IT on **delayed ischemic neurological deficits (DIND)** after aSAH	Rate of delayed ischemic neurological deficit (DIND), defined as **clinical deterioration caused by delayed cerebral ischemia (i.e., a new focal neurological deficit or decline on the Glasgow Coma Scale of 1 point not attributable to other causes)** on days 3–21
To assess the effect of the IT on the development of post-hemorrhagic hydrocephalus	Rates of shunt-dependent **hydrocephalus** at 6 months following aSAH
To assess the effect of the IT on sonographic vasospasm	**Delta mean flow velocities** of both middle cerebral arteries—measured by transcranial Doppler ultrasonography on days 3–21
To assess the effect of the IT on the need for endovascular interventions for the treatment of cerebral vasospasm	Rate of **endovascular interventions** for the treatment of cerebral vasospasm
To assess the effect of the IT on the course of intensive care therapy	**Key parameters of intensive care medicine (Sequential Organ Failure Score)**
To assess the effect of the IT on **morphological brain damage**	**Morphological brain damage** at 6 months after aSAH as assessed by MRI
To assess the effect of the IT on further clinical and surrogate outcomes	NIHSS score at days 3–21 and at 6 months
	Key parameters of **endocrinological dysfunction**
	**Key markers of neuronal injury and systemic inflammation in patient blood**
	**Electroencephalographic patterns as measured by continuous EEG monitoring during intensive care period (exploratory endpoint)**
To assess the **safety of the IT**	**Safety of IT:** (serious) adverse events related to the IT

### Trial design {8}

This is a mono-center, randomized, controlled, parallel-group, open-label phase II trial. Fifty-four patients will be randomized at a ratio of 1:1 to receive either standard of care or standard of care plus the IT (Fig. 1).

**Fig. 1 Fig1:**
[figure not shown]
Study design

## Methods: participants, interventions, and outcomes

### Study setting {9}

Patients with severe aSAH (WFNS ≥3) will be enrolled at the Medical Center, University of Freiburg, a large academic tertiary care center in Southern Germany. Patients will be recruited from the population of patients referred to our institution.

Both groups will receive the required emergency treatment, most notably securing of ruptured brain aneurysm(s) by microsurgical clipping or endovascular coiling, as soon as possible after admission to hospital, prior to randomization, i.e., independent of trial participation. Likewise, the decision for placement of an external ventricular drain (EVD) will be made as medically indicated, i.e., as part of routine treatment outside of the trial. The same is true for the evaluation of intracranial pressure (ICP). In our institution, all patients with severe aSAH usually receive invasive ICP monitoring.

### Eligibility criteria {10}

Patients eligible for inclusion in this trial must meet all the inclusion criteria and none of the exclusion criteria listed in Table 2.

**Table 2 Tab2:** In-/exclusion criteria

**Inclusion criteria**	1. Male or female patients aged ≥18 years and < 80 years 2. Modified Fisher grade 3 or 4 3. Cisternal/ventricular blood amount according to Hijdra score ≥ 20 4. Admission WFNS grade ≥ 3 (if grade 5 only with fixed dilated pupil due to raised ICP for less than 45 min) 5. External ventricular drain (EVD) in situ or indication for placement of EVD 6. Disease duration ≤96 h before randomization 7. Written informed consent, either by the patient or by the patient’s legally authorized representative 8. Cerebral aneurysm as a definitive source of subarachnoid hemorrhage 9. Patients in whom the cerebral aneurysm has been safely treated via open surgical or endovascular technique
**Exclusion criteria**	1. Pregnancy 2. Surgical contraindications according to the opinion of the investigator 3. Inability to administer study medication (known allergy to urokinase or nimodipine) 4. Presence of a severe illness prior to aSAH (e.g., progressive cancer, terminal organ failure, severe neurological disorder, life expectancy < 1 year) 5. Known and persistent abuse of medication or drugs 6. Presence of severe cerebral infarction related to the aSAH or medical procedures prior to randomization 7. Presence of intracerebral hematoma that is ≥30 ml (assessed using the AxBxC/2 method) or in eloquent location prior to randomization 8. Presence of a condition or abnormality that in the opinion of the investigator would compromise the safety of the patient 9. Known severe complications during aneurysm securing (e.g., dissections of blood vessels, vessel occlusions, re-hemorrhage) 10. Clinical signs of brain stem/midbrain compression (dilated pupil not reacting to light) persisting for more than 45 min at any time between aSAH onset and randomization 11. Persons who are in a relationship of dependence/employment with the sponsor or the investigator 12. For MRI follow-up: cardiac pacemaker and/or cardiac defibrillator. Stent implantation within the last 6 weeks prior to MRI, claustrophobia

### Who will take informed consent? {26a}

Written informed consent will be obtained for every subject participating in this clinical trial. However, most of the patients will not be able to give informed consent initially due to the severity of the underlying aSAH. Therefore, three different informed consent procedures will be distinguished in this trial:
Patient’s own informed consentInformed consent by the patient’s legal representativePatient’s presumed consent

The patient’s own informed consent will be obtained whenever possible. If this is not possible, consent by the patient’s legal representative will be obtained. If neither of the two is possible, the patient may be included based on his/her presumed consent.

An authorized investigator will be responsible for explaining the nature, significance, implications, expected benefits, and potential risks of the clinical trial and alternative treatments to the patient or his/her representative and for obtaining written informed consent.

To include a patient into the study based on presumed consent, the following preconditions must be met:
The patient him-/herself is unable to provide informed consent.A legal representative is not in place and cannot be established in adequate time.An emergency situation as per the German Medicines Act (section 41) is given.

As additional precautionary measures to be taken in such a case, the patient’s presumed will must be determined, e.g., by consulting the patient’s next of kin. Furthermore, an independent physician who is not involved in the trial must be present during the discussion for determining the patient’s presumed will.

If a patient’s trial inclusion has initially been based on consent by a legal representative or on presumed consent, the patient’s own written informed consent will be obtained as soon as the patient’s condition allows for an informed decision.

### Additional consent provisions for collection and use of participant data and biological specimens {26b}

Patients or their legal representatives will be given the opportunity to voluntarily provide additional consent (opt-in) for having blood samples stored in a local biobank (see item {33} for details).

## Interventions

### Explanation for the choice of comparators {6b}

The safety and efficacy of the IT are to be investigated as an add-on to the best available medical treatment as per applicable treatment guidelines and institutional routine.

### Intervention description {11a}

Patients randomized to group 1 will receive standard-of-care treatment for patients with aSAH according to the European guidelines [18]. Continuous ICP monitoring will be performed throughout aSAH treatment in order to detect pathological increases of ICP.

Patients randomized to group 2 will receive standard-of-care treatment plus additional IT. Essentially, the IT consists of a sequential cisternal lavage with urokinase for 7 days starting from randomization, then with Ringer’s solution for another 4 to 14 days, and with nimodipine anytime between randomization and day 21 in case of verified or suspected CVS, administered via a stereotactically implanted catheter. Ringer’s solution will be used as a carrier solution for the other two investigational medicinal products (IMPs), urokinase and nimodipine, and as a third IMP. A graphic overview of the therapy protocol in group 2 is provided in Fig. 2 and a detailed dosing regimen in Table 3.

**Fig. 2 Fig2:**
[figure not shown]
Therapy protocol in group 2

**Table 3 Tab3:** Dosing regimen of investigational medicinal products

Study medication	Pharmaceutical form and route of administration	Duration/regimen
Urokinase diluted in Ringer’s solution	Intrathecal use	Continuous cisternal lavage with 100 I.U. urokinase per ml Ringer’s solution at a rate of ~ 50 ml/h for 7 days following implantation of the catheter, i.e., from day 2 ± 2 until day 9 ± 2 after aSAH, or until the onset of cerebral vasospasm or DIND. Total daily dose: 120.000 I.U. Note: urokinase administration has to be stopped when nimodipine is given.
Nimodipine diluted in Ringer’s solution	Intrathecal use	Nimodipine is given on demand in case of vasospasm (i.e., delayed ischemic neurological deficit or mean flow velocities of any intracranial vessel > 120 cm/s on Doppler ultrasonography). In this case, nimodipine is administered as continuous cisternal lavage with 0.005 mg nimodipine per ml Ringer’s solution at a rate of ~ 50 ml/h. Nimodipine infusion is performed from the onset of vasospasm to the cessation of vasospasm, at least, however, for 24 h. If necessary, nimodipine can be administered as often as necessary or for extended periods during aSAH treatment (up to the entire aSAH treatment phase of this trial, i.e., up to 21 days). Total daily dose: 6 mg. Note: urokinase administration has to be stopped when nimodipine is given.
Ringer’s solution	Intrathecal use	Continuous cisternal lavage with Ringer’s solution at a rate of ~ 50 ml/h, starting from day 9 ± 2 (i.e., from the end of urokinase therapy) to day 18 ± 3 after aSAH; the exact stop date will be determined based on the investigator’s risk-benefit assessment for the individual patient. The criteria for this assessment are risk of catheter infection, macroscopic clearance of lavage fluid (i.e., no or minimal residual xanthochromia), and individual risk assessment for the development of vasospasm beyond day 15, considering patient neurological status, WFNS grade, sex, age, blood amount, and course of transcranial Doppler ultrasonographic measurements.

The application of the IT requires a stereotactic neurosurgical intervention (STX-VCS) for catheter placement after aneurysm securing and randomization (on day 2 ± 2, usually day 2 or 3, ≤96 h after aSAH). Pre- and postoperative imaging (cCT) will be performed for the planning of surgery, verification of appropriate catheter position, and ruling out postoperative complications.

The STX-VCS procedure has been described in detail elsewhere [17, 19]. In the present clinical trial, the STX-VCS catheter is used for infusion of the IMPs, thus representing the inflow tract. A separate EVD—given to every patient with severe aSAH as a matter of clinical routine—represents the outflow tract. Figure 3 shows a schematic drawing of the setup during the administration of the IT.

**Fig. 3 Fig3:**
[figure not shown]
Setup of investigational treatment administration. Arrows indicate the flow direction of the lavage solution

### Criteria for discontinuing or modifying allocated interventions {11b}

Investigators must follow the protocol for administering the IT whenever possible. However, modifications may be permitted when the patients’ safety or well-being is concerned. Table 4 lists the details on the modifications that will be permitted and under which circumstances.

**Table 4 Tab4:** Modification of investigational treatment

Event/problem	Permitted modification
Procedure-related undesired effect, i.e., attributable to physical/mechanical effects of intrathecal fluid application	Reduction of infusion rate while maintaining the doses of the IMPs.
Undesired effect that is potentially attributable to pharmacological effects of urokinase or nimodipine	Reduction in doses of these drugs or lavage with Ringer’s solution only.
Occurrence of intracranial hemorrhage after stereotactic catheter implantation and administration of IMP	• Evaluation of whether hemorrhage is related to IMP administration, related to the application procedure, or due to other causes (e.g., due to aneurysm re-bleed, secondary aneurysm rupture, surgical procedures, hemorrhagic transformation of cerebral infarction, spontaneous). • Termination of urokinase and nimodipine if administration of these IMPs is the most likely cause of intracranial hemorrhage. It will not be recommenced until deemed safe by the investigator. • Lavage with Ringer’s solution only if deemed safe by the investigator. • If relatedness to IMPs considered unlikely by the investigator: evaluation of potential benefits and risks of continuation of the IMPs; continued administration of IMPs if benefits of continuation are assumed to outweigh the risks.
Occurrence of raised intracranial pressure (ICP > 20 mmHg)	If considered related to IT administration: termination until normalization of ICP; continued administration of IMPs if deemed safe by the investigator.
Occurrence of cardiac symptoms (e.g., brady- or tachycardia, arrhythmias, electrocardiographic abnormities)	• If graded as serious and if potentially induced by the IT, administration of the IMPs is paused immediately and may be continued with or without dose modifications and changes in infusion rates. • If graded as non-serious but related to the IT: continuation of IT with dose modifications and/or changes in infusion rates.
Occurrence of headache	Reduction of IMP doses and/or infusion rates if considered attributable to the IT.
Normal route of lavage (intracranial infusion via the cisternal STX-VCS catheter and outflow via the EVD) not possible, e.g., due to impaired outflow	Reversed flow direction (i.e., EVD in, cisternal catheter out).
Lavage therapy not feasible at the intended infusion rate	Lower infusion rate or small volume bolus lavage therapy.
Particular clinical circumstances (e.g., recurrent intracranial hemorrhage, persisting intraventricular/intracerebral/subarachnoid blood clots, refractory cerebral vasospasm, cerebral vasospasm lasting beyond day 21)	Recommencement and/or dose modifications of intrathecally administered urokinase or nimodipine.

### Strategies to improve adherence to interventions {11c}

As this is a trial involving intensive care patients, adherence to the intervention protocols in the treatment phase lies primarily with the investigators.

### Relevant concomitant care permitted or prohibited during the trial {11d}

Concomitant anticoagulant therapy must be discontinued for the stereotactic procedure. Otherwise, there are no restrictions regarding concomitant treatment.

### Provisions for post-trial care {30}

Treatment and imaging follow-up after the end of the trial (e.g., for long-term aneurysm surveillance) will be performed according to the trial site’s routine. Otherwise, post-trial treatment is at the discretion of the treating physician. As given by the German Medicines Regulation, an insurance cover exists for all trial participants for compensation to those who suffer harm from trial participation.

### Outcomes {12}

The primary endpoint is the proportion of subjects with a favorable outcome as measured on the Modified Rankin Scale (mRS) at 6 months after aSAH, assessed by an independent physician. mRS will be analyzed in a dichotomized fashion:
Favorable, defined as mRS 0–3 (independent)Unfavorable, defined as mRS 4–6 (dependent/dead)

Secondary endpoints are provided in Table 1.

### Participant timeline {13}

A comprehensive visit flowchart detailing all study-related assessments and their schedule is presented in Additional File 1.

### Sample size {14}

The sample size calculation is based on the primary endpoint dichotomized mRS (mRS > 3) with an expected proportion of 50% in the standard-of-care group and 15% in the experimental treatment group. These assumptions are based on the first results of individual off-label treatments with the new procedure as described by [name] et al. [17, 19].

The study is planned to detect a difference between the experimental and control groups with respect to dichotomized mRS (mRS > 3) with a power of 80% using the two-sided *χ*^2^ test at a two-sided significance level of 5%. The null hypothesis is rejected if the asymptotic two-sided 95% confidence interval for the odds ratio (control vs. experimental) does not contain one. Under these assumptions, 54 patients are required for analysis.

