## Statistical methods

### Statistical methods for primary and secondary outcomes {20a}

The effects of the experimental vs. control intervention with respect to the primary endpoint will be estimated in the intention-to-treat (ITT) population by logistic regression. As an estimate of the effect size, the odds ratio will be given with a corresponding asymptotic two-sided 95% confidence interval. The two-sided test on the difference between the two trial arms at significance level 5% will be based on the corresponding asymptotic two-sided 95% confidence interval from the logistic regression model. Data should be collected regardless of the patient’s adherence to the protocol, especially on the clinical outcome, to obtain the best approximation to the full analysis set. Data should also be collected on other therapies received post-dropout. Specifically, full details of the type of additional (non-randomized) therapy given, including when and for how long it was used and at what dose, should be collected. In case of missing values for the primary endpoint, this will be handled by multiple imputation [20].

Secondary endpoints will be analyzed descriptively using regression models. Treatment effects will be calculated with two-sided 95% confidence intervals. Details will be specified in the statistical analysis plan (SAP) which will be finalized after the end of the recruitment period, but before the start of the final analysis.

Safety analyses will be performed in the safety set including all patients for whom one of the treatments was started. All safety parameters (e.g., adverse events, laboratory assessments) will be listed by the patient and displayed in summary tables. The adverse events (AEs) are displayed in summary tables by treatment as follows.

The total number of AEs; the minimum, maximum, and mean number of AEs per patient; the total number of follow-up days (number of days in the observation period); the number of AEs per FU-day; the number of patients who had at least one AE; and the number of patients who stopped treatment due to AE will be given.

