### Methods for additional analyses (e.g., subgroup analyses) {20b}

Not applicable, no subgroup or adjusted analysis is planned.

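### N = 54 and the 80% power were computed for the chi-square test, but the primary hypothesis is decided by an asymptotic odds-ratio interval whose type is not named; if it is Wald, exact power is 78.3% and a zero cell blocks rejection

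*Protocol article*

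**What the plan says.** Protocol article, Sample size {14}: the calculation concerns unfavourable outcome (mRS > 3) "with an expected proportion of 50% in the standard-of-care group and 15% in the experimental treatment group". The trial is planned "with a power of 80% using the two-sided" chi-square "test at a two-sided significance level of 5" percent. The next sentence gives the decision rule: "The null hypothesis is rejected if the asymptotic two-sided 95% confidence interval for the odds ratio (control vs. experimental) does not contain one". The section ends: "Under these assumptions, 54 patients are required for analysis".

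Trial design {8} sets the allocation: "Fifty-four patients will be randomized at a ratio of 1:1", so 27 per arm.

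Statistical methods for primary and secondary outcomes {20a} repeats the decision rule. The two-sided 5% test "will be based on the corresponding asymptotic two-sided 95% confidence interval from the logistic regression model". Missing primary outcomes are to be multiply imputed.

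Methods for additional analyses {20b}: "no subgroup or adjusted analysis is planned". The logistic model therefore contains treatment only and reduces to the 2×2 table.

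**The concern.** The test behind the sample size is not the rule that will decide the trial. Chi-square and the logistic interval agree in large samples. Here, however, only about 4 unfavourable outcomes are expected in the experimental arm (27 × 0.15 = 4.05), and at that count they can differ.

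Two things are at stake on the trial's single confirmatory test. First, the stated 80% may not be the power of the stated rule. Second, a data set that is significant by the test used for sizing may be declared negative. The extreme case is an experimental arm with no unfavourable outcome: the log odds ratio and its standard error diverge, and a Wald interval cannot exclude one.

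**Working it through.** **Inputs.** Unfavourable proportions 0.50 (control) and 0.15 (experimental), two-sided 5%, 80% power, all from Sample size {14}. 27 per arm, from Trial design {8}. No covariates, from {20b}.

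**1. Reproduce the plan's figure.** Pooled-variance formula without continuity correction, mean proportion 0.325:

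n = [1.96·√(2 × 0.325 × 0.675) + 0.8416·√(0.50 × 0.50 + 0.15 × 0.85)]² / 0.35² = 26.9, so 27 per arm and 54 in total.

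The continuity-corrected formula gives 33 per arm and the unpooled one 25. N = 54 therefore belongs to the uncorrected Pearson chi-square, whose approximate power at 27 per arm is 80.2%.

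**2. Exact power of each candidate rule.** Sum the binomial probabilities over all 28 × 28 possible tables, counting those in which the rule rejects. For Wald, reject if |log OR| / √(1/a + 1/b + 1/c + 1/d) > 1.96; a table with a zero cell counts as no rejection, because the standard error is infinite.

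| Rule, 27 per arm | Exact power, 50% vs 15% | Exact size at common rate 0.325 | Maximum exact size |
|---|---|---|---|
| Pearson chi-square | 82.0% | 5.3% | 5.7% |
| Wald interval | 78.3% | 4.4% | 4.4% |
| Profile-likelihood interval | 82.8% | 5.8% | 8.8% |

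The 8.8% occurs at low common event rates; at a common rate of 0.15 the profile-likelihood size is 6.1%. With 28 per arm the exact Wald power is 80.2%.

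**3. Disagreement between chi-square and Wald.** Under the design assumptions, chi-square rejects and Wald does not with probability 3.6%. The reverse never occurs. Two examples (control vs experimental):

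- 13/27 vs 6/27. Chi-square = 54 × (13×21 − 6×14)² / (27 × 27 × 19 × 35) = 3.98, p = 0.046. OR = (13×21)/(6×14) = 3.25; standard error of log OR = √(1/13 + 1/14 + 1/6 + 1/21) = 0.602; Wald interval 0.998 to 10.58, no rejection.
- 9/27 vs 3/27. Chi-square p = 0.0495; OR 4.00, Wald interval 0.95 to 16.93, no rejection.

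The likelihood-ratio statistics for these tables are 4.05 and 4.00, both above 3.84. A profile-likelihood interval would reject in both.

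**4. Zero cell.** P(0 of 27 in the experimental arm) = 0.85²⁷ = 0.0124, or 1.2%. For 13/27 vs 0/27, chi-square = 54 × (13×27)² / (27 × 27 × 13 × 41) = 17.1, yet the Wald rule cannot reject. This accounts for about a third of the 3.6% disagreement (1.2/3.6).

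**The case against.** **Wald is inferred.** The article never uses the word. A profile-likelihood interval from the same model is also asymptotic, has 82.8% power and copes with a zero cell. This stands, and every Wald figure here is conditional on that reading. It does not remove the point: the wording admits two intervals that give opposite verdicts on 13/27 vs 6/27, and the profile-likelihood version has a size problem of its own.

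**The effect is small and errs on the safe side.** This also stands. The shortfall against 80% is 1.7 points. The 3.6-point gap is measured against the exact Pearson power of 82.0%, which the protocol never claims. Wald keeps its exact size below 5%, while Pearson exceeds it slightly. The uncertainty in the assumed 50% and 15% probably matters more than 1.7 points of power.

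**Interval type and zero-cell handling often go into the SAP.** Fair, and their absence alone would be no finding. The mismatch between the sizing test and the decision rule, however, is written into the protocol itself.

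Three stronger readings are tempting, and the documents do not support them:

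- *That there are two competing primary tests.* Chi-square appears only as the sizing basis. Both places that say how the hypothesis is decided give the interval.
- *That power is really 74.5% and N should be 62.* Those figures come from the log-odds-ratio normal approximation, which overstates the loss here. Exact enumeration gives 78.3%, and 56 patients suffice for 80%.
- *That nothing covers missing outcomes, because 54 are needed for analysis and 54 are randomized.* Section {20a} plans multiple imputation and outcome collection regardless of adherence, death is scored as mRS 6, and {18b} reports good follow-up experience. Only N is not inflated.

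**Conclusion.** The point holds as a mismatch of minor to moderate weight. N = 54 and 80% power are correct for the uncorrected chi-square test, but that test does not decide the trial. If the deciding interval is Wald, its exact power is 78.3%. It then contradicts the sizing test in one direction with probability 3.6%, and it cannot register the most favourable possible result in the experimental arm (probability 1.2%).

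These figures assume 27 evaluable patients per arm, true rates of 50% and 15%, no covariates, and no rejection when a cell is zero. The sample size is not grossly wrong and the type I error is not inflated under Wald. What should be settled before the data are seen is which interval decides the trial and what happens with a zero cell.

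**What to change.** Make the decision rule and the sizing basis the same, in one of two ways:

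1. **Preferred.** Base the primary decision on the uncorrected chi-square (score) test used for sizing, and report the odds ratio with the score interval obtained by inverting that test. Test and interval then always agree, and a zero cell is handled. The cost is a maximum exact size of about 5.7%, against 4.4% for Wald. The sponsor should accept this openly in advance.
2. **Keep the Wald interval.** Name it, restate the power as about 78% with all 54 patients evaluable, and prespecify a fallback for a zero cell.

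A Firth penalised profile likelihood is an acceptable alternative if logistic regression is to remain the vehicle (exact power 81.3%, maximum size 5.4%, handles zero cells), but it is not required.

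Each option is a sentence or two in the protocol, repeated in the SAP, using standard methods and no extra patients. It should be fixed before outcome data are reviewed.
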